## Abstract

**Background:**

HIV/AIDS is one of the most serious problems in many parts of the world, and is a high priority for health managers and decision-makers. The aim of the qualitative part of this study will be to develop a mobile SMS (short messaging services) counselling intervention to prevent HIV/AIDS, while the quantitative part will be to test the effectiveness of a mobile SMS counselling intervention to improve the knowledge, attitude, and practices of patients concerning the prevention of HIV/AIDS.

**Method:**

A mixed methods approach will be used. Qualitative part: *Design:* focus group discussions (FGDs) will be conducted. *Setting:* Hospital/NGOs in Terengganu, Malaysia. *Participants:* Three FGDs will be conducted with male and female HIV/AIDS patients, and one group of local community leaders. One FGD will be conducted for each group. Three in-depth interviews (IDIs) will be conducted with patients who had HIV/AIDS, of which one will be female. Quantitative part: *Design:* a cluster randomized clinical trial with 384 HIV/AIDS patients in Terengganu, Malaysia. *Intervention:* Mobile SMS counselling intervention for patients concerning the prevention of HIV/AIDS.

**Results:**

The main outcomes of this study will be the differences in knowledge, attitude, and practices of patients concerning the prevention of HIV/AIDS between the baseline and immediate follow-up after the intervention, and after 3 months.

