## Methods/design

The main objective of this study is to develop, implement, and assess the effectiveness of the mobile SMS counselling intervention to improve the knowledge, attitude, and practices of HIV/AIDS patients concerning HIV/AIDS prevention in Malaysia. The specific objectives are given below: to assess the patients initial response to mobile SMS counselling intervention in terms of acceptability, feasibility, and sustainability; to develop mobile SMS counselling intervention for HIV/AIDS prevention; to identify factors associated with the willingness to read text messages on HIV/AIDS prevention in Malaysia; to determine the socio-demographic and environmental factors, level of knowledge, attitude, and practices of patients on HIV/AIDS prevention; to develop and implement a Mobile SMS counselling HIV/AIDS prevention intervention to improve the knowledge, attitude, and practices of HIV/AIDS patients; to determine the association among the socio-demographic factors and environmental factors with knowledge, attitude, and practices of HIV/AIDS patients about HIV/AIDS prevention at the baseline and post intervention; to compare the mean scores for knowledge, attitude, and practices among HIV/AIDS patients between the intervention and the control group at the baseline and post intervention (within group and between groups); and to evaluate the effectiveness of Mobile SMS counselling intervention among HIV/AIDS patients to improve the knowledge, attitude, and practices concerning HIV/AIDS.

The hypotheses are given below: There is an association between the willingness to read text messages and HIV/AIDS patients in Malaysia; there is no significance in the socio-demographic and environmental factors, level of knowledge, attitude, and practice of patients concerning HIV/AIDS prevention; there is an association between the social-demographic and environmental factors, and the knowledge, attitude, and practices of HIV/AIDS patients concerning HIV/AIDS prevention at baseline and post-intervention; there is a significant difference in the mean scores for the knowledge, attitude, and practices of HIV/AIDS patients between the intervention and control group at the baseline and post-intervention (within and between groups), and the application of Mobile SMS counselling intervention to improve the impact of the HIV/AIDS prevention knowledge, attitude, and practices among patients, between the intervention and the control group.

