The research questions are given below: What are the socio-demographic and environmental factors associated with the knowledge, attitude, and practice of HIV/AIDS patients? What is the difference in the mean scores for the knowledge, attitude, and practices of HIV/AIDS patients concerning HIV/AIDS prevention for the intervention and control groups? And what is the impact of Mobile SMS counselling intervention on the knowledge, attitude, and practices of HIV/AIDS patients?

This is a mixed methods research. The first phase will be a qualitative study to develop a mobile SMS counselling intervention concerning the knowledge, attitude, and practices of patients concerning HIV/AIDS prevention, while the second phase will be a quantitative study to implement and evaluate the effectiveness of a mobile-based counselling intervention concerning the knowledge, attitude, and practices of patients in respect of HIV/AIDS prevention. Three focus group discussions (FGDs) will be conducted with 6 male HIV/AIDS patients with FGDs, 6 female HIV/AIDS patients with FGDs, 10 community leaders from a village with FGDs, and three in-depth interviews (IDIs) will be conducted with 3 HIV/AIDS patients. The second phase, the cluster randomized clinical trial, will be carried out for approximately 12 months from September 2019 to July 2020. The hospital/NGOs (or cluster) will be the unit of randomization, and an equal number of hospitals/NGOs will be randomized to one of the two arms. This phase includes a Community trial and pre- and post-assessment through face-to-face interviews using a semi-structured questionnaire (Fig. 1). The study population will be HIV/AIDS patients in the Kuala Terengganu and Kuala Nerus districts of Malaysia. A complete list of HIV/AIDS patient registration will be collected from the Hospitals/NGOs in Kuala Terengganu and Kuala Nerus districts from January 2018 to March 2019. The sampling units will be individual patients who are admitted into the Hospital/NGOs between January 2018 and March 2019 and who are eligible according to the inclusion criteria for this study. The criteria for inclusion in this study include all persons diagnosed with HIV ≥ 18 years of age. Patients excluded from this study are those patients who are HIV positive but diagnosed with psychiatric disorders and are mentally incapacitated. The sample size estimation formula for hypothesis testing of the two-group comparison is used [13]:

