**Fig. 2 Fig2:**
[figure not shown]
Schematic diagram of the development of the intervention module

The control group patients will not receive any SMS during the study periods, but the usual information received from the mass media (newspaper, TV, Radio) or any campaign for HIV/AIDS prevention. However, they will receive the SMS counselling intervention about HIV/AIDS after data collection.

The Statistical Package for Social Science (SPSS) version 22 will be used to analyse the data. Data will be collected, checked, cleaned, and data entry will be conducted carefully and successfully. Factors with a statistically significant association with the socio-demographic and environmental variables on HIV/AIDS prevention knowledge, attitude, and practices will be identified at the baseline, immediate post intervention, and after 3 months follow up in the logistic model (ρ-value of 0.05) controlling for other variables. To determine the significant difference between the intervention and the control groups, a t-test and chi-square test will be used. To identify the impact of two different interventions, 2-way repeated measure ANOVA and one-way ANOVA will be used.

The main findings are given below: development of mobile SMS based counselling intervention for prevention of HIV/AIDS with FGDs; identification of implementation process for mobile SMS based counselling intervention for prevention of HIV/AIDS patients; development of tools for measuring the effectiveness of Mobile SMS based counselling intervention for prevention of HIV/AIDS patients; development of an effective intervention for HIV/AIDS patients in a low resource setting to improve the knowledge, attitude, and practices concerning HIV/AIDS prevention, and assessment of the effectiveness of a mobile SMS based counselling intervention programme on the HIV/AIDS prevention knowledge, attitude, and practices of HIV/AIDS patients.

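### The main-outcome sentence omits the arm comparison, and the hypotheses list within-group change and a baseline difference beside the valid between-arm contrast, with none marked as the main one

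*Protocol article*

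**What the plan says.** The abstract's Results section gives the main outcomes as differences in knowledge, attitude and practice (KAP) scores "between the baseline and immediate follow-up after the intervention, and after 3 months". The sentence does not mention the control arm.

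Methods/design has an objective that compares mean scores "between the intervention and the control group at the baseline and post intervention (within group and between groups". The matching hypothesis predicts a significant difference "between the intervention and control group at the baseline and post-intervention (within and between groups". Taken literally, this pair covers change within each arm, a difference between arms at baseline and a difference between arms after the intervention.

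Other sentences in Methods/design do compare the arms:
- The last hypothesis concerns impact on "knowledge, attitude, and practices among patients, between the intervention and the control group".
- A research question asks about the difference in mean scores "concerning HIV/AIDS prevention for the intervention and control groups".
- The analysis paragraph after Fig. 2 states: "To determine the significant difference between the intervention and the control groups, a t-test and chi-square test will be used".
- For the impact of the intervention, the same paragraph says "2-way repeated measure ANOVA and one-way ANOVA will be used".

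Control patients get no SMS until data collection is over, but do get "the usual information received from the mass media (newspaper, TV, Radio) or any campaign for HIV/AIDS prevention". Assessment before and after the intervention is by face-to-face questionnaire interview.

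**The concern.** Two of the listed contrasts do not measure what the SMS programme does.

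- **Change within an arm.** This adds together any SMS effect, the media and campaigns that the plan says continue, any time trend, and the effect of being interviewed again on the same topics. The control arm is there to subtract everything except the first.
- **A difference between arms at baseline.** This arises before any message is sent, so it carries no information about the SMS effect. The plan nevertheless predicts that it will be significant.

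The plan does not rank these contrasts below the valid one, and the sentence that defines the main outcomes describes a pre-post difference only. A team could follow the text, find a significant gain in the SMS arm and report that the main outcome was met, whatever happened in the control arm. The abstract's Conclusions section already asserts that the intervention will be effective, so the wording should leave no such route.

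**Working it through.** **Step 1. The contrasts side by side.** Write the mean KAP score as S0 and S1 (SMS arm, baseline and follow-up) and C0 and C1 (control arm). Let d be a drift common to both arms and e the SMS effect. With sound randomisation and recruitment, S0 and C0 have the same expectation.

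| Contrast | Where it appears | Expected value |
|---|---|---|
| S1 − S0 | Abstract, Results (literal reading); Methods/design objective and hypothesis (within group) | d + e |
| C1 − C0 | Same | d |
| S0 − C0 | Methods/design objective and hypothesis (baseline, between groups) | 0 |
| S1 − C1 | Methods/design objective, hypothesis and research question; t-test | e |
| (S1 − S0) − (C1 − C0) | Available from the 2-way repeated-measures ANOVA (arm-by-time term) | e |

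Only the last two rows isolate e. Both are within reach of the plan. However, the t-test and chi-square sentence names no time point, the ANOVA sentence does not name the arm-by-time term, and the main-outcome sentence points at the first row.

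**Step 2. Inputs for size.** The article gives no figure on this point to reproduce. From its sample-size paragraph:
- 174 patients per group before attrition (87 × 2). It is used here only as the planned number per arm; the derivation of the 87 is a separate matter.
- Two-sided alpha 0.05 (z = 1.96).
- Design effect 1 + 19 × 0.05 = 1.95, which the article rounds to 2.

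Assumptions not in the article: no SMS effect (e = 0), common drift d of 0.1 to 0.3 SD, within-person correlation ρ of 0.3 to 0.7, equal SD at both visits.

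**Step 3. Chance that a within-arm test is significant when e = 0, clustering ignored.**

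SE of mean change, in SD units = √(2(1 − ρ)/174):
- ρ = 0.3: √(1.4/174) = 0.0897
- ρ = 0.5: √(1.0/174) = 0.0758
- ρ = 0.7: √(0.6/174) = 0.0587

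Probability = Φ(d/SE − 1.96) + Φ(−d/SE − 1.96):

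| d (SD) | ρ = 0.3 | ρ = 0.5 | ρ = 0.7 |
|---|---|---|---|
| 0.1 | 20.0% | 26.1% | 39.9% |
| 0.2 | 60.6% | 75.1% | 92.6% |
| 0.3 | 91.7% | 97.7% | 99.9% |

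For example, with d = 0.2 and ρ = 0.5, d/SE = 0.2/0.0758 = 2.64 and Φ(2.64 − 1.96) is about 75%.

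**Step 4. Sensitivity to clustering.** Dividing 174 by 1.95 leaves an effective 89.2 per arm. The ranges over ρ become about 13-23% (d = 0.1), 36-68% (d = 0.2) and 67-96% (d = 0.3). This is approximate, since the design effect for a change score need not equal that for a single score.

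**Step 5. The between-arm contrast under the same assumptions.** Its expected value is d − d = 0, so a test that allows for clustering rejects at its nominal 5% whatever the drift.

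**The case against.** The strongest reply is that the control arm is well represented in the plan. The same hypothesis covers the post-intervention comparison between arms, the last hypothesis and a research question compare the arms, and the analysis paragraph specifies between-arm tests and a repeated-measures ANOVA whose arm-by-time term estimates the effect. This stands. A reader might infer from the main-outcome sentence that the trial has no valid test of the SMS effect or intends to discard its control arm; the article does not support that. The sentence is also one line of an abstract, and change from baseline is a legitimate outcome variable once it is compared between arms. What remains is that no valid contrast is marked as the main one and that the sentence defining the main outcomes leaves the comparison out.

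The baseline wording may be loose English for the cells of a group-by-time table. That is possible, but as written it predicts a significant difference at baseline.

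A reader might add that any baseline difference must be chance because the trial is randomised. That is too strong here. Hospitals/NGOs are randomised, not patients, and the article does not settle whether patients are enrolled before or after their site is allocated, so imbalance could also reflect recruitment. Either way it says nothing about the SMS effect. Nor does the article say that baseline tests will be used to choose covariates or to judge the randomisation, so that harm should not be attributed to it.

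One could also quote a rate of spurious baseline findings. Three independent tests at 5% give 1 − 0.95³ = 14%. The figure reaches 1 − 0.84³ = 41% only if clustering is ignored, at about 16% error per test. Most of the larger figure therefore belongs to a different problem, and this point does not rest on it.

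Finally, the drift and correlation are assumed. That is correct, and the results vary widely with them.

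**Conclusion.** The point holds as a defect of definition and ranking, not as the absence of a valid analysis. The main-outcome sentence omits the arm comparison. The objective and hypothesis set within-group change and a baseline difference level with the one contrast in that list that estimates the SMS effect. A pre-post gain in the SMS arm would literally satisfy the stated main outcome.

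The textual part rests on the article alone. The size is an illustration: with no SMS effect, a within-arm test is significant in about 20-40%, 61-93% or 92-99.9% of trials for a shared drift of 0.1, 0.2 or 0.3 SD (correlation 0.3 to 0.7, 174 per arm, clustering ignored). Discounting the sample for the plan's own design effect lowers these figures, but every one stays well above 5%. The plan should be changed on this point.

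**What to change.** 1. Restate the main outcome as the difference between arms in mean score at follow-up, adjusted for the baseline score and allowing for clustering by hospital/NGO, and say which follow-up it refers to. Use the same wording in the abstract, the objective and the hypothesis.
2. Delete the hypothesis of a between-arm difference at baseline. Describe baseline characteristics and scores by arm instead.
3. Keep within-arm changes as description only, and state that they do not support a claim of effectiveness.

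The cost is wording plus a clustered, baseline-adjusted model for the main comparison. Data collection does not change, because the baseline score is already measured. Adjustment should also help precision: with equal SDs and clustering set aside, the variance relative to comparing follow-up scores alone is 1 − ρ², that is 0.91, 0.75 and 0.51 for ρ of 0.3, 0.5 and 0.7.

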**Conclusions:**

The mobile based SMS counselling intervention developed will be effective in improving the knowledge, attitude, and practices of patients concerning HIV/AIDS prevention in Terengganu, Malaysia.

**Trial registration:**

Thai Clinical Trials Registry, TCTR20200212001; 7/02/2020.

## Background

According to the World Health Organization, approximately 35 million people worldwide are infected with HIV/AIDS and it appears that the disease will be identified as the most important cause of death in the world by 2020 [1]. In Malaysia, the country’s epidemic was mostly pushed by people who injected drugs (PWID) at an early stage, but this sample shifted towards increasing sexual transmission with the PWID/sexual transmission ratio decreasing from 4 in 2000 to 0.2 in 2015. People who inject drugs (PWID), female sex workers (FSW), transgender human beings (TG), and men who have sex with men (MSM) are identified as being the most affected widespread populations, with changes for infection exceeding 5%. The vast majority of them are above 25 years of age [2].

HIV challenges a person physically, socially, and psychologically. HIV is further recognized as a relatively stigmatized disorder [3]. In addition, it can additionally threaten a sense of meaning, purpose, and significance in life [4]. HIV causes people to become infected with physical and psychological problems [5]. In this regard, it is difficult for PLHIV to admit the truth that they are infected with HIV [6], which contributes to self-denial [7] and hinders any correction in their behaviour [8].

HIV/AIDS is among the diseases that not only affects the physical aspects, but also the social and psychological conditions of patients [9]. In addition to the physiological effects of the disease, people living with HIV/AIDS (PLWHA) may encounter numerous problems, such as discrimination, losing social status and role, changes in the patterns of relationships (intimacy), losing jobs and financial resources, and facing problems to provide the required medicines [10]. Many of these problems are also common among other people who suffer from other chronic diseases, but the stress associated with social and family problems arising from the diseases, such as social stigma and exclusion, especially by support groups, is intensely and uniquely threatening to people with HIV/AIDS [11]. Community and social network members may fear being infected with the HIV disease and they are frightened of taking care of HIV/AIDS patients [12].

HIV/AIDS is one of the diseases that currently affect not only the physical aspects, but also the social and psychological conditions of patients [9]. In addition to the physiological effects of the disease, people living with HIV/AIDS (PLWHA) may face serious problems, such as discrimination, loss of social status and roles, change in relationship patterns (intimacy), loss of work and economic resources, and problems in obtaining the required medications [10]. Many of these problems are more frequent than those faced by other people who are struggling with other chronic diseases, as it is not just the ailment, it is the stress associated with social and home troubles, such as social stigma and exclusion in particular, as some of those providing assistance and help groups are intensely and exceptionally threatened by people with HIV/AIDS [11]. Community and social network participants may fear that they will be infected with HIV, other ailments, and are afraid of caring for patients with HIV/AIDS [12].

However, there has been a lack of research on the challenges of life among people affected with HIV (PAWH) based on the mode of HIV transmission, and, hence, this study examines the different experiences and challenges of life among the participants based on the mode of transmission. The aim of this research is a trial to test the efficacy of a MOBILE SMS based counselling intervention for the prevention of HIV/AIDS in Malaysia.

## Methods/design

The main objective of this study is to develop, implement, and assess the effectiveness of the mobile SMS counselling intervention to improve the knowledge, attitude, and practices of HIV/AIDS patients concerning HIV/AIDS prevention in Malaysia. The specific objectives are given below: to assess the patients initial response to mobile SMS counselling intervention in terms of acceptability, feasibility, and sustainability; to develop mobile SMS counselling intervention for HIV/AIDS prevention; to identify factors associated with the willingness to read text messages on HIV/AIDS prevention in Malaysia; to determine the socio-demographic and environmental factors, level of knowledge, attitude, and practices of patients on HIV/AIDS prevention; to develop and implement a Mobile SMS counselling HIV/AIDS prevention intervention to improve the knowledge, attitude, and practices of HIV/AIDS patients; to determine the association among the socio-demographic factors and environmental factors with knowledge, attitude, and practices of HIV/AIDS patients about HIV/AIDS prevention at the baseline and post intervention; to compare the mean scores for knowledge, attitude, and practices among HIV/AIDS patients between the intervention and the control group at the baseline and post intervention (within group and between groups); and to evaluate the effectiveness of Mobile SMS counselling intervention among HIV/AIDS patients to improve the knowledge, attitude, and practices concerning HIV/AIDS.

The hypotheses are given below: There is an association between the willingness to read text messages and HIV/AIDS patients in Malaysia; there is no significance in the socio-demographic and environmental factors, level of knowledge, attitude, and practice of patients concerning HIV/AIDS prevention; there is an association between the social-demographic and environmental factors, and the knowledge, attitude, and practices of HIV/AIDS patients concerning HIV/AIDS prevention at baseline and post-intervention; there is a significant difference in the mean scores for the knowledge, attitude, and practices of HIV/AIDS patients between the intervention and control group at the baseline and post-intervention (within and between groups), and the application of Mobile SMS counselling intervention to improve the impact of the HIV/AIDS prevention knowledge, attitude, and practices among patients, between the intervention and the control group.

The research questions are given below: What are the socio-demographic and environmental factors associated with the knowledge, attitude, and practice of HIV/AIDS patients? What is the difference in the mean scores for the knowledge, attitude, and practices of HIV/AIDS patients concerning HIV/AIDS prevention for the intervention and control groups? And what is the impact of Mobile SMS counselling intervention on the knowledge, attitude, and practices of HIV/AIDS patients?

This is a mixed methods research. The first phase will be a qualitative study to develop a mobile SMS counselling intervention concerning the knowledge, attitude, and practices of patients concerning HIV/AIDS prevention, while the second phase will be a quantitative study to implement and evaluate the effectiveness of a mobile-based counselling intervention concerning the knowledge, attitude, and practices of patients in respect of HIV/AIDS prevention. Three focus group discussions (FGDs) will be conducted with 6 male HIV/AIDS patients with FGDs, 6 female HIV/AIDS patients with FGDs, 10 community leaders from a village with FGDs, and three in-depth interviews (IDIs) will be conducted with 3 HIV/AIDS patients. The second phase, the cluster randomized clinical trial, will be carried out for approximately 12 months from September 2019 to July 2020. The hospital/NGOs (or cluster) will be the unit of randomization, and an equal number of hospitals/NGOs will be randomized to one of the two arms. This phase includes a Community trial and pre- and post-assessment through face-to-face interviews using a semi-structured questionnaire (Fig. 1). The study population will be HIV/AIDS patients in the Kuala Terengganu and Kuala Nerus districts of Malaysia. A complete list of HIV/AIDS patient registration will be collected from the Hospitals/NGOs in Kuala Terengganu and Kuala Nerus districts from January 2018 to March 2019. The sampling units will be individual patients who are admitted into the Hospital/NGOs between January 2018 and March 2019 and who are eligible according to the inclusion criteria for this study. The criteria for inclusion in this study include all persons diagnosed with HIV ≥ 18 years of age. Patients excluded from this study are those patients who are HIV positive but diagnosed with psychiatric disorders and are mentally incapacitated. The sample size estimation formula for hypothesis testing of the two-group comparison is used [13]:
$$ \mathrm{N}={\left\{\mathrm{Z}1-\upalpha /2\ \sqrt{2}\tilde{\mathrm{P}}\left(1-\tilde{\mathrm{P}}\right)+\mathrm{Z}1-\upbeta \sqrt{\mathrm{P}}1\left(1-\mathrm{P}1\right)+\mathrm{P}2\left(1-\mathrm{P}2\right)\right\}}^2/{\left(\mathrm{P}1-\mathrm{P}2\right)}^2 $$

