**Fig. 1 Fig1:**
[figure not shown]
Study flow diagram showing the key components of the intervention

### N = 87

Where P1 = HIV Prevalence in 2012 = 0.189 & P2 = HIV Prevalence in 2014 = 0.163 [2]. P̃ = (P1 + P2)/2 = 0.176. Z1 – α/2 = standard error when α = 0.05 (95% confidence interval) = 1.96, and Z1 – β = standard error associated with power = 0.842 (β = 0.20) and Power (1 – β) = 80%.

As participants are nested within in villages, a potential design effect needs to be considered. The assumed number of participants per hospital/NGOs is 20, and an intra-cluster correlation coefficient of 0.05 can be expected. This would result in a design effect = 1 + (m-1) × ICC = 1 + (20–1) × 0.05 = 2. Based on the above formula, the required minimum sample size for each group, n is **174.** To factorise in 10% attrition (32), the total required per group is **192**; hence, a total of **384** patients will be required for the sample in both groups.

Figure 2 below shows a schematic diagram for the development of the intervention module used in this study. The module will be developed through the process of consultation with a group of experts who will include one professor of statistics, one expert in behavioural intervention, one senior medical doctor, and one HIV/AIDS specialist (Fig. 2). The mobile based SMS counselling intervention aims to increase the knowledge, attitude, and practices of patients concerning HIV/AIDS prevention in Malaysia. The SMS will be developed by the researcher based on FGDs and a literature review. It uses informal language and will be sent weekly on Friday, which is a holiday. These factors have been shown to have an impact and positively affect the message acceptability when using SMSs for sexual health promotion [14, 15]. Mobile phones and the Internet are popular everywhere in Malaysia, and are well-liked by people, so the study aims to determine whether they would be effective and improve patient’s knowledge, attitude, and practices concerning HIV/AIDS prevention.

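### The only stated allocation restriction is an equal number of sites per arm; with about 20 hospitals and NGOs, drawing within site type would guard cheaply against an uneven hospital/NGO mix

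*Protocol article*

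**What the plan says.** Methods/design fixes the unit: "The hospital/NGOs (or cluster) will be the unit of randomization". It then gives the allocation rule: "an equal number of hospitals/NGOs will be randomized to one of the two arms". The catchment covers two districts: "The study population will be HIV/AIDS patients in the Kuala Terengganu and Kuala Nerus districts of Malaysia".

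The sample-size paragraph under Fig. 1 sets the cluster size, "The assumed number of participants per hospital/NGOs is 20", and the between-site variation, "an intra-cluster correlation coefficient of 0.05 can be expected". The total is 384 patients, 192 per arm.

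The article does not give the number of sites or how many are hospitals and how many NGOs. It mentions no stratification, matching or other restriction by site type or district, and does not rule one out. It does not say that outcomes differ between hospital and NGO patients.

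On analysis, Methods/design plans t-tests and chi-square tests between arms, plus one-way and two-way repeated measures ANOVA. No site-type term is named for these comparisons. The Abstract (Results) defines the main outcomes as differences between baseline and the two follow-up points. The objectives in Methods/design also include comparing mean scores between arms after the intervention.

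**The concern.** The stated rule equalises a count of sites, and those sites are of two visibly different kinds. With few sites, an equal count does not secure a similar mix: one arm can hold most of the hospitals and the other most of the NGOs.

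If site type predicts knowledge, attitude or practice, part of any post-intervention difference between arms would then reflect who was recruited where. A reader could not easily separate that from the effect of the SMS intervention. The allocation is made once, and site type is known before it, so the draw is the natural place to deal with this.

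**Working it through.** **Number of sites.** The article's chain from 87 per group is 87 × 2 = 174, then 174 × 1.1 = 191.4, taken up to 192, so 384 in total. At 20 patients per site, 384/20 = 19.2, or about 20 sites, 10 per arm. This takes the 384 as given. Whether 87 follows from the stated proportions is a separate matter: the standard formula gives 3,367 per group. A larger trial would have more sites and less chance imbalance.

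**Chance of an uneven mix.** With H hospitals among 20 equal-sized sites and 10 sites drawn per arm, the number of hospitals in one arm is hypergeometric. There are C(20,10) = 184,756 possible draws.

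- 10 hospitals, 10 NGOs, split 7:3 or worse: 2 × (14,400 + 2,025 + 100 + 1)/184,756 = 0.179.
- 6 hospitals, 14 NGOs, split 5:1 or worse: 2 × (6 × 2,002 + 1,001)/184,756 = 0.141.

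In both cases the hospital share differs by at least 40 points (70% against 30%, or 50% against 10%). H is not in the article, so the range is shown; values above 10 mirror these with the two types exchanged.

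| Hospitals among 20 sites | Gap ≥ 20 points | Gap ≥ 40 points | All hospitals in one arm |
|---|---|---|---|
| 10 | 65.6% | 17.9% | under 0.1% |
| 9 | 37.0% | 7.0% | under 0.1% |
| 8 | 65.0% | 17.0% | 0.1% |
| 7 | 35.0% | 5.7% | 0.3% |
| 6 | 62.8% | 14.1% | 1.1% |
| 5 | 30.3% | 3.3% | 3.3% |
| 4 | 58.2% | 8.7% | 8.7% |
| 3 | 21.1% | 0 | 21.1% |
| 2 | 47.4% | 0 | 47.4% |
| 1 | 0 | 0 | 100% |

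The figures alternate because an odd H allows only odd gaps in site count. With 18 sites, a gap of four or more sites (at least 44 points) has probability 5.7% with 9 hospitals, 15.3% with 8 and 13.1% with 6.

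**Drawing within type.** The gap becomes 0 sites if H is even and 1 site (10 points) if H is odd.

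**How large a site-type difference the ICC allows.** A difference of d SD between types, with a proportion p of sites being hospitals, contributes p(1 − p)d² of the total variance. This cannot exceed the ICC of 0.05.

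- 10/10: 0.25d² ≤ 0.05, so d ≤ 0.45. If type explains half of the ICC, 0.25d² = 0.025 and d = 0.32.
- 6/14: 0.21d² ≤ 0.05, so d ≤ 0.49. At half, d = 0.35.

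**Shift in post-intervention arm means at a 40-point gap (0.4 × d).**

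- 10/10: 0.13 SD (half of the ICC) to 0.18 SD (all of it).
- 6/14: 0.14 SD to 0.20 SD.

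For scale, the standard error of an arm difference with 192 per arm and design effect 1.95 is √(2 × 1.95/192) = 0.14 SD. The shift is about one standard error.

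**Cost of a site-type term.** It uses one cluster-level degree of freedom. With 20 sites the two-sided 5% critical t moves from 2.101 to 2.110. With 8 sites it moves from 2.447 to 2.571, and with 4 from 4.303 to 12.706.

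**Adjusting after an uneven draw.** At 7:3 the correlation between arm and type is 0.40, so the variance rises by a factor 1/(1 − 0.16) = 1.19. At 5:1 the correlation is 0.44 and the factor is about 1.24. That is like losing about 3 to 4 of 20 sites (20 − 20/1.19 = 3.2; 20 − 20/1.24 = 3.9).

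**The case against.** **Silence is not a decision.** A reader might infer that the draw is definitely unstratified. The article does not establish this. It condenses a fuller protocol, its flow diagram is not shown, and its rule could be read as equal numbers of each type. The slash is used elsewhere as one label for a cluster, as in "The assumed number of participants per hospital/NGOs is 20", so a single pool is the more natural reading, but not the only one. This stands, and it makes the fix conditional.

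**The harm is assumed.** Nothing says hospital and NGO patients differ in outcome, and they share one set of eligibility criteria. This also stands. The ICC shows only that the authors expect sites to differ, not that type is the reason. A round figure such as 0.5 SD is tempting but would use more than the whole ICC (0.25 × 0.25 = 0.0625 at 10/10; 0.21 × 0.25 = 0.0525 at 6/14).

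**Baseline is measured.** A stable difference in level between site types cancels in change from baseline and in the arm-by-time comparison. This stands for those analyses. It does not cover the planned between-arm comparisons of post-intervention means by t-test, where a level difference remains.

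**Confounding.** A reader might infer that site type biases the allocation. It does not. Chance imbalance under a valid random draw costs precision and credibility, and between-site variation is already part of the design effect.

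**Adjustment is available.** It would be wrong to say that adjusting afterwards recovers little. It works, at the price of roughly a fifth to a quarter more variance at the splits considered.

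**Conclusion.** The point holds as a recommendation to improve the stated allocation rule, not as a demonstrated error. On about 20 equal sites, a pooled draw gives a gap of 40 points or more in hospital share in at most 18% of draws (10 of each type), 14% with 6 hospitals and 14 NGOs, and less often or never for some other mixes. Gaps of 20 points are common.

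At a 40-point gap and a 10/10 mix, post-intervention arm means would shift by up to about 0.18 SD, or about 0.13 SD if type explains half of the ICC. Change from baseline would be affected less. The upper figure requires that sites of the same type do not differ at all.

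The conclusion rests on four assumptions: the total of 384, equal sites of 20, no stratification in the full protocol, and a link between site type and outcome. It should not be read as saying that stratifying is entirely free or removes every imbalance. It balances site counts rather than patient counts, and it does nothing if one type has a single site.

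**What to change.** Unless the full protocol already does so:

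- Randomise hospitals and NGOs in separate strata, half of each to each arm, with a pre-set rule for an odd number in a stratum.
- Include site type as a factor in the arm comparison.
- Report the number of hospitals and NGOs in each arm.

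Methods/design places the trial phase between September 2019 and July 2020. If allocation has already taken place, the draw should stand: report the split by arm and adjust for site type.

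If the full protocol does stratify, one sentence in the article settles the point.

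The cost is one sentence, a second allocation list and one cluster-level degree of freedom, which is negligible with 20 sites. If the actual number of sites is very small, the lost degree of freedom matters and should be weighed before a site-type term is fixed in the analysis.
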